### The Control Condition – IBS Support Group

We selected a social-support group intervention led by master's level social workers as the control condition. This format was selected to control for subject credibility, expectations, and attention, providing regular group contact, a group leader, and a structure similar to the Mindfulness Program group, while excluding the active elements of the Mindfulness Program. A similar control condition was used successfully in a previous study testing the effectiveness of cognitive behavior therapy for the treatment of IBS [22]. In that study, the Support Group arm was found to produce an *expectation *of benefit comparable to the cognitive behavior therapy group but less actual change in IBS symptoms than cognitive behavior therapy.

In parallel with the Mindfulness Program, the Support Group sessions consist of one 2-hour session each week for 8 consecutive weeks plus one half-day Saturday session during the second half of the intervention. The half-day session involves the preparation and sharing of an "IBS-friendly" meal by Support Group participants.

Weekly Support Group sessions focus on specific pre-designated topics and involve open group discussions about subjects' experiences with, or reaction to, the topic. Session topics, in the following order, include: (a) reasons for attending the Support Group; (b) personal experience of IBS symptoms; (c) triggers for IBS symptoms; (d) medical concerns related to IBS assessment or treatment; (e) changes in IBS symptomatology over time; (f) the impact of diet and exercise on IBS; (g) social relationships and IBS; and (h) review of the Support-Group experience.

Each session begins with an introduction of the specific IBS-related topic by the group leader. Subjects are encouraged to provide examples from their own life experiences to enhance each other's understanding of the topic. Although Support Group leaders facilitate discussion and answer questions, they do not give didactic information, behavioral prescriptions, or advice. Instead, the role of the group leader is to prompt participants with questions, facilitate discussion, and maintain an environment where disclosure is possible. To that end, leaders ask open ended questions, and promote discussion by using probes such as asking for clarification, requesting explanations, and encouraging cross-talk between group members. If subjects ask the group leader a direct question about how to manage their IBS symptoms, the group leader responds by redirecting the question to the group and urging participants to share their own coping strategies with one another.

Homework assigned each week throughout the course includes readings from the provided text, *"IBS for Dummies*" [29]. Subjects are asked to write a journal entry about the discussion topic for the coming week as it relates to their personal experience with IBS, as well as to keep a daily diary of IBS symptoms. Subjects may choose to record journal/diary information either electronically (submitted daily) or on paper (submitted weekly at the meetings or mailed).

### Outcome measures and study instruments (See Table 1)

**Table 1 T1:** Measures for the Mindfulness and Support Group Subjects

Construct	Measure	Administration
***Primary Outcome measure***		

Symptom Severity	Irritable Bowel Symptom Severity Scale	Pre, 2 wk, 3 mo, 6 mo, 12 mo post

***Secondary Outcome measures***		

Symptom frequency	Daily Symptom Diary	Daily during the intervention and for 2 weeks post

IBS-related anxiety	Visceral Sensitivity Index	Pre, 2 wk, 3 mo, 6 mo, 12 mo post

Economic impact of IBS	The Work Productivity and Activity Impairment for IBS (WPAI: IBS)	Pre, 2 wk, 3 mo, 6 mo, 12 mo post

Co-Morbid Symptoms	Recent Physical Symptoms Questionnaire (RPSQ)	Pre, 2 wk, 3 mo, 6 mo, 12 mo post

General psychological distress	Brief Symptom Inventory (BSI)	Pre, 2 wk, 3 mo, 6 mo, 12 mo post

Anger and its expression	The State-trait Anger Expression Inventory (STAXI)	Pre, 2 wk, 3 mo, 6 mo, 12 mo post

Maladaptive coping methods	Coping Strategies Questionnaire (CSQ)	Pre, 2 wk, 3 mo, 6 mo, 12 mo post

Quality of life specific to IBS	IBS-QOL	Pre, 2 wk, 3 mo, 6 mo, 12 mo post

***Effect modification measures***		

Expectancy of success of intervention	Borkovec and Nau credibility scales	Prior to second session

Catalogue of distressing prior events	Family Inventory of Life Events (FILE)	Pre intervention only

Demographics	Age, race, education, marital status, income	Pre intervention only

***Process measures***		

Measure of mindfulness: Multiple constructs	Five Facet Mindfulness Questionnaire (FFMQ)	Pre, 2 wk, 6 mo, 12 mo post

Measure of mindfulness: Acceptance construct	Toronto Mindfulness Scale	Pre, 2 wk, 6 mo, 12 mo post

Administration of the outcome and process measures for Specific Aims 1 and 2 takes place upon entry into the study, at the completion of the 8-week programs, and again at 3, 6, and 12 months after program completion. Collection of these data requires approximately one hour of subject time at each of the 5 measurement visits.

#### Primary outcome variable

##### Irritable Bowel Symptom Severity Scale (IBSS)

The IBSS is a validated brief measure of IBS severity. Responders rate retrospectively, for the past 10 days, abdominal pain severity and frequency (separate ratings), bloating severity, dissatisfaction with bowel habits and life interference from bowel symptoms. These five ratings are totaled to obtain an overall rating of IBS severity. The IBSS has been shown to be valid and reliable [1]; it was found to discriminate IBS patients from controls, and to discriminate between patients categorized as mild, moderate, and severe by independent clinical assessment. In a study of 1603 patients with functional bowel disorders including 815 who met Rome II criteria for IBS [30], the IBSS correlated well (Spearman's rho = .66; p < .0001) with the Functional Bowel Disease Severity Index [1] and also correlated with the frequency of medical clinic visits for IBS in the prior 6 months (r = .21; p < 001). In their systematic review of outcome measures in IBS clinical trials, Bijkerk and colleagues ranked the IBSS as one of the two best outcome measures for IBS trials based on psychometric properties [31].

#### Secondary outcome variables

##### Daily Gastrointestinal Symptom Diary

The symptom diary was adapted from Blanchard et al. [32] Subjects are asked to complete daily symptom ratings on the Internet, using a password-protected web page, or on a paper version of the same diary. On separate 0–4 scales, subjects rate how much of a problem they have had in the past day with abdominal pain and tenderness, constipation, diarrhea and bloating. They are also asked to record whether symptoms interfered with eating, drinking or their usual activities, and how many minutes they did homework related to the study. A space is provided for other comments.

##### Brief Symptom Inventory-18 (BSI-18)

The BSI is an 18-item version of the Symptom Checklist-90-R (SCL-90-R) [33]. Subjects rate how much they were bothered in the last 7 days by each of 18 symptoms, including separate scores for anxiety, depression, somatization, and a global symptom severity index. The BSI has good internal consistency reliabilities (Cronbach's alpha = 0.71–0.85) and test-retest reliabilities (α = 0.68 – 0.91) as well as excellent convergent validity with the SCL-90-R (r = 0.92–0.98) [34].

##### IBS-Quality of Life (IBS-QOL)

The IBS-QOL questionnaire is a 34-item disease-specific quality-of-life scale that measures changes in physical and psychosocial functioning as a result of IBS. It is responsive to change over 12 weeks [35] and has high internal consistency (Cronbach's alpha = .95) and high reproducibility over a 7-day interval (ICC = .86) [30].

##### State-trait Anger Expression Inventory (STAXI)

This is a 44-item questionnaire that measures State Anger and Trait Anger [36]. Internal consistency for State and Trait Anger is good (α = 0.86–0.93) and it correlates well with hostility indices on the MMPI [37]. In a test of the effectiveness of an 8-week meditation intervention for patients with chronic low back pain, the State Anger measures decreased from pre- to post-intervention: F(1,15) = 3.38, p = 0.09 [38].

##### Visceral Sensitivity Index (VSI)

The VSI is a 15-item scale which measures anticipatory anxiety with respect to the likely occurrence of symptoms such as abdominal pain [39]. Internal consistency is excellent (Cronbach's α = 0.93, inter-item correlation = 0.47), and the VSI shows good convergent validity with the Hospital and Depression (HAD) Anxiety subscale (r = 0.73) and the Anxiety Sensitivity Index (ASI) (r = 0.66). Regression analysis revealed that the VSI is a strong predictor of symptom severity, accounting for 24% of the variance [39].

##### Recent Physical Symptoms Questionnaire (RPSQ)

This 26-item scale was developed by the UNC Center for Functional Gastrointestinal and Motility Disorders by systematically reviewing the literature to identify the somatic symptoms reported with increased frequency by patients with IBS [40]. Patients are asked to rate the frequency of occurrence of these symptoms in the last 30 days on a 5-point ordinal scale. The internal consistency (Cronbach's alpha) for this questionnaire is 0.86. The RPSQ correlates strongly with number of physician visits in the past year (r = .62).

##### Work Productivity and Activity Impairment for IBS (WPAI: IBS)

The WPAI: IBS measures work-time lost and activity impairment secondary to IBS. The WPAI: IBS was evaluated for accuracy and validity with 135 IBS patients in 2004 [41]. The sum for missed work time in a retrospective diary was predictive of the WPAI: IBS score. Test-retest correlations were high (r = 0.97 – 0.99) as well [41].

##### Coping Strategies Questionnaire (CSQ)

The 50-item CSQ was designed to assess coping strategies used by patients who have chronic illness [42]. The 6-item Catastrophizing subscale, the most frequently used subscale, has excellent internal consistency (alpha = .91) and correlates with measures of pain intensity and functional impairment. Three other subscales – Distraction, Ignoring Pain Sensations, and Distancing from Pain – have good internal consistency reliability (α = 0.80 – 0.83) and contain items that may distinguish between the two groups at outcome, in terms of coping styles.

#### Moderators

##### Demographics

The study is limited to women. The demographic questionnaire collects data about each woman's age, marital status, race/ethnicity, years of education, approximate family income, and medical history related to IBS.

##### Family Inventory of Life Events and Changes (FILE)

The FILE was designed to assess the accumulation of stressful events experienced by a family [43]. Reliability is well established for the full scale (α = 0.72 – 0.81), although the subscales are not as stable. Test-retest reliability for the full scale is good (r = 0.72 – 0.77).

#### Evaluation of Subject Expectation/Bias and Protocol Variability

##### Credibility scale (Attitude Towards Treatment Questionnaire)

This measure was based on the original measure by Borkovec and Nau which assesses patients' expectations of benefit once treatment has been explained [25]. The scale has been found to distinguish between standard psychotherapy approaches and illogical placebo treatments, it is predictive of clinical improvement, and it is relatively independent of symptom severity. Although originally designed to focus upon treatments for fear, Drossman, Toner, and Whitehead modified the questions to target psychological (and placebo) treatments of functional gastrointestinal disorders [44].

##### Quality Control (See Table 2)

**Table 2 T2:** Quality Control and Feasibility Measures

Component	Measure	Responsible party
Context	Log of comments about space, contacts with other interested parties outside of participants	Instructors Study coordinator

Dose delivered	Attendance log Enrollment diary	Instructors Study coordinator

Dose received	Participant log of adherence to homework assignments	Instructors

Fidelity	Video-taping of instructors delivering interventions	Research assistant, PI

Instructors record attendance, logistical problems and other study-related issues. The study coordinator keeps a similar log of logistical issues and contacts subjects not completing the intervention to evaluate factors leading to dropout. To evaluate subject engagement, subjects are prompted to keep a log of their homework practice in their daily diaries.

To evaluate intervention fidelity, we measure instructor adherence to protocol through videotaping the second and seventh Mindfulness Program and IBS Support Group sessions with an unmanned stationary video recorder. Video-taping is for purposes of identifying variations in instructor attitude, communication bias and systematic variations in behavior between treatment groups. It is also used to assess adherence to protocol as well as to screen for any group-dependent differences in content or style of communication between the instructor and participants.

#### Process Measures

##### Five Facet Mindfulness Questionnaire (FFMQ)

The FFMQ was developed by Baer based on exploratory and confirmatory factor analyses of five existing questionnaires designed to explore constructs of mindfulness identified in prior research [45]. The resulting instrument is a 39-item, Likert-type measure assessing five identified facets of mindfulness: non-reactivity to inner experience; non-judging of inner experience; acting with awareness; describing; and observing. Individual facets of the FFMQ correlate positively with openness to experience, emotional intelligence, and self compassion, and negatively with alexethymia, dissociation, and psychological distress [45].

##### Toronto Mindfulness Scale

The Toronto Mindfulness Scale adapted by J. Kristeller measures the acceptance construct in mindfulness. The scale is currently undergoing reliability and validity testing [23].

#### Adverse events

All subjects are asked to record any adverse events in their diaries and to report them to the group leaders, the study coordinator or the study physician. In addition, they are asked about their experiences weekly at the training sessions. Subjects are also strongly encouraged to discuss with the research staff anything they feel to be an adverse event or other issues that are problematic for them about the study.

### Analytic strategy

#### Sample Size and Power Calculation

Outcome measures for clinical trials were investigated, including a report of adequate relief of IBS symptoms and the magnitude of symptom reduction on the IBSS, our primary outcome in this trial [46]. Based on this data, patients reporting "adequate relief," defined here as a clinically meaningful outcome, showed a reduction in IBSS scores of 87 units. The power to detect this change at α = .05 in samples of 30 per group is approximately 84%. In the current study, 45 subjects per group is planned.

Regression modeling will be used to test the primary hypothesis. A simple linear regression model with the IBSS score at the end of the study controlling for IBSS score at the baseline will be used to test for significant treatment effects. We will use repeated measures analysis on IBSS measures to detect whether the change in IBSS scores differ significantly between the two groups. Because of the correlated nature of the repeated measures, regression models using a generalized estimating equations (GEE) approach will be used to test the hypothesis of change. A significant time and treatment interaction will detect significant changes in the score. A similar analysis strategy using GEE methods will be used to analyze daily records of IBS symptoms. All data analysis will be performed on an intent-to-treat basis. The GEE method assumes that missingness in data are completely at random. Under the missing at random assumption, it is possible to conduct analyses using multiple imputation procedures [47].

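### The primary IBSS hypothesis has two unranked significance tests, an end-of-study score tied to no visit, and inconsistent timing of the first post-treatment assessment

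*Protocol article*

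**What the plan says.** The Hypotheses section gives a single primary hypothesis: greater improvement on the IBSS with the Mindfulness Program than with the Support Group. It names no time point.

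Under Sample Size and Power Calculation, the article says regression will test this hypothesis and then describes two analyses:

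- "A simple linear regression model with the IBSS score at the end of the study controlling for IBSS score at the baseline", used to test for treatment effects.
- "We will use repeated measures analysis on IBSS measures to detect whether the change in IBSS scores differ significantly between the two groups", fitted by GEE, with a significant time-by-treatment interaction as the criterion.

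The timing of the IBSS is given in three places:

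- Table 1, primary outcome row: "Pre, 2 wk, 3 mo, 6 mo, 12 mo post".
- The text below Table 1: on entry, "at the completion of the 8-week programs, and again at 3, 6, and 12 months after program completion".
- Background: end of treatment, then 3, 6 and 12 months.

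On the recall period, the IBSS description says: "Responders rate retrospectively, for the past 10 days".

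The power statement reads "The power to detect this change at α = .05 in samples of 30 per group is approximately 84" percent, for a clinically meaningful outcome in which patients "showed a reduction in IBSS scores of 87 units". It then says: "In the current study, 45 subjects per group is planned".

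**The concern.** Both analyses carry a significance criterion for the same outcome, and no sentence says which one decides. They can disagree. The regression compares the groups at one visit, while the interaction compares their patterns over five assessments. An early gain that fades could show in one and not in the other.

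The visit matters as much as the test. A post-treatment score measures short-term response and a 12-month score measures durability. If the visit and test are settled only after the data are seen, a reader cannot tell which question the trial set out to answer, and the nominal 5% is not assured.

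The first post-treatment assessment raises a separate issue of what is measured. With a 10-day recall, an assessment at program completion looks back over the last classes. One taken 2 weeks later looks back only over time after the program.

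**Working it through.** **1. Does the power statement settle the test or the visit?** Inputs from the article: difference 87, n = 30 per group, α = .05, power about 84%. No standard deviation is given, so 84% cannot be reproduced, only inverted. For a two-sided two-sample comparison (normal approximation):

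power = Φ(87 / (SD × √(2/30)) − 1.960) = 0.84

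so 87 / (SD × 0.2582) = 1.960 + 0.994 = 2.954, and SD = 87 / (2.954 × 0.2582) ≈ 114. With the noncentral t the SD is about 112. One-sided, it is about 126 to 128. The figure is therefore attainable with an assumed SD, but the statement names neither test nor visit and does not resolve the ambiguity.

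**2. What could the end of the study mean?** Literally, the last assessment, at 12 months. But the Abstract says 66 women have completed or are completing the interventions, and the Discussion says the same 66 have completed or are completing the study. The article thus uses the two terms interchangeably, so the post-treatment assessment is also a supported reading. That makes two candidate visits.

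**3. What does the recall cover?** At program completion, the past 10 days include at least the last weekly class. At 14 days after completion, they run from day 14 − 10 = 4 to day 14, all after the program. Both descriptions contain five assessments in total (one baseline, four later), so this is one assessment described two ways and not an extra one.

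**4. Type I error if more than one result may count.** For two independent tests it is 1 − 0.95² = 9.75%. The tests here share data, so a null simulation was run. Assumptions, none of them from the article:

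- complete normal data at five assessments;
- exchangeable correlation 0.5 to 0.7;
- 45 per group (the plan) or 33 per group (an even split of the 66 remaining; withdrawals were in fact 14 and 7);
- the GEE interaction represented by a 4-df test of change from baseline (time categorical) or a linear slope (time continuous), since the article does not say how time is coded.

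There were 8,000 runs per scenario, with a repeat at 100,000 runs as a check:

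| What counts as success | 8,000 runs | 100,000 runs |
|---|---|---|
| One pre-named test | 4.6–5.5% | 4.8–5.1% |
| Regression post-treatment, or 4-df interaction | 8.4–9.2% | 8.6–8.8% |
| Regression at 12 months, or 4-df interaction | 8.5–9.0% | 8.6–8.8% |
| Regression post-treatment, or slope interaction | 9.5–10.4% | 9.5–9.9% |
| Regression at 12 months, or slope interaction | 7.2–7.9% | 7.4–7.7% |
| Regression at either visit, or 4-df interaction | 11.9–12.5% | 12.0–12.2% |
| Regression at either visit, or slope interaction | not run | 11.6–12.0% |

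Values just above 10% in the smaller run are simulation noise, since two 5% tests cannot jointly exceed 10%. In round figures the error is about 7% to 10% with one visit and either test, and about 11% to 13% with either visit as well.

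**The case against.** The strongest reply is that the regression comes immediately after the sentence on the primary hypothesis and is the primary test, and that the GEE addresses a differently worded question about change. Pairing an endpoint comparison with a trajectory analysis is ordinary practice, and an article may leave ranking to the analysis plan. This has weight, and a missing label alone would be no finding. But GEE is also regression, it is given its own significance criterion on the same outcome, and even on this reading the regression has no identified visit.

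Three stronger readings are tempting and not supported:

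- A reader might infer that the 5% error rate is already lost. The article nowhere says that success on either test suffices, so the inflation is conditional.
- A reader might count all four post-baseline visits as candidates. Nothing makes the 3- or 6-month visit the end of the study.
- A reader might treat 2 weeks versus completion as another route to significance. It is one assessment with inconsistent wording; the Background and the text below Table 1 may simply describe the 2-week assessment loosely. It affects what is measured, not the number of tests.

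Nor can a loss of power from a fading effect be quantified, because the documents give no effect at any visit.

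Two mitigating facts stand. The stated primary aim is feasibility, with results meant to guide later trials. Staff handling data input and analysis are to be masked, which limits data-driven choice but does not control the error from two tests.

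**Conclusion.** The point holds at moderate severity. The article gives its one primary hypothesis two unranked significance tests, ties the regression to a visit that can be read as post-treatment or 12 months, and describes the first post-treatment assessment inconsistently. These are features of the stated text and not merely omitted detail.

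If either test could count, the error rate would be about 7% to 10% instead of 5%; if either visit could also serve, about 11% to 13%. Both ranges depend on the simulation assumptions above and on an either-counts rule that the article does not state. Feasibility as the primary aim reduces the consequence but does not remove it, because the efficacy hypothesis still carries α = .05 and a power claim.

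**What to change.** Before the final analysis:

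1. Replace the end-of-study wording with one named visit. The post-treatment visit of Table 1 is a reasonable choice, but the sponsor should confirm which visit is intended.
2. Name as the single primary test, at two-sided 5%, the baseline-adjusted between-group difference in IBSS at that visit, taken either from the regression or as one contrast from the repeated-measures model.
3. Make the time-by-treatment interaction and the other visits secondary or supportive.
4. Reconcile the Background, Table 1 and the text below Table 1 with when the first post-treatment questionnaire is actually collected, so that the 10-day recall period is clear.
5. State which test and visit the 84% power refers to, and the standard deviation used.

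The cost is wording only: the article reports that recruitment is continuing and that the final analysis is not yet available. The downside is that the sponsor gives up the choice of time point and test.

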### Screening, consent, and enrollment

Prospective subjects are screened by telephone by the study coordinator. If an individual is eligible for the study and wishes to participate, the study coordinator schedules a meeting at a mutually convenient time and location to explain the study, obtain informed consent, and complete initial assessments. A psychosocial assessment and gastrointestinal medical questionnaire is completed at this visit or shortly thereafter. Subjects are told that they may have to wait a short time for classes to begin while additional subjects are being recruited. Classes are scheduled to begin when a minimum of 6 subjects have been randomized to each of the two groups.

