### The Intervention Group – Mindfulness for Irritable Bowel Syndrome

The mindfulness-based stress and pain management program (Mindfulness Program) was based on the Mindfulness-Based Stress Reduction (MBSR) program developed by Jon Kabat-Zinn and Saki Santorelli at the University of Massachusetts. MBSR is a flexible program, adaptable to a variety of patients with wide-ranging symptoms [26]. The modification introduced was to emphasize symptoms and perceptions concerning IBS when teaching about mindfulness, as well as in group discussion. For example, it is suggested to participants that they might notice any sensations in the abdominal area and distinguish those sensations from thoughts *about *sensations. In so doing, the mindfulness intervention targets maladaptive cognitive coping styles such as catastrophizing, which have been shown in the literature to exacerbate irritable bowel symptoms [27,28].

In keeping with the MBSR program, the Mindfulness Program consists of one 2-hour session each week for 8 consecutive weeks plus a Saturday retreat near the end of the intervention. For the Saturday retreat setting of the Day of Mindfulness, we shortened the length of the day from six to four hours to match the length of time of the Support Group's Saturday session.

#### Class 1

The course begins with personal introductions to create group cohesion, an overview of the coming eight weeks, and a discussion of attitudes that support mindfulness. Participants are led through an experiential exercise that focuses on the immediacy of physical sensations and differentiates sensations from thoughts *about *sensations; they are encouraged to take this practice home as mindful eating. They are introduced to diaphragmatic breathing. Participants are then led through a lengthy scan of body sensations to facilitate non-judgmental awareness; this exercise is also assigned as part of routine home practice, along with weekly readings of relevant chapters in *"Full Catastrophe Living" *and "*IBS for Dummies."*

#### Class 2

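### Both arms are taught in groups, but the named models take no account of correlation within a class, so standard errors are too small if such correlation exists

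*Protocol article*

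**What the plan says.** **Delivery.** Under Screening, consent, and enrollment: "Classes are scheduled to begin when a minimum of 6 subjects have been randomized to each of the two groups". No maximum or average class size is given. Women are randomised individually (Randomization), then treated together. Each arm has eight weekly group sessions plus one Saturday session. For the Mindfulness arm, "The course begins with personal introductions to create group cohesion". The Support Group section describes leader-facilitated discussion in which women are encouraged to talk to each other and pass on coping strategies. Under Study Benefits, the article expects that women may learn from one another how to manage IBS.

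**Analysis.** The section Sample Size and Power Calculation names, for the primary hypothesis, "A simple linear regression model with the IBSS score at the end of the study controlling for IBSS score at the baseline". It adds a longitudinal analysis: "Because of the correlated nature of the repeated measures, regression models using a generalized estimating equations (GEE) approach will be used". It mentions no class or leader term, no ICC and no design effect.

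**Power.** The effect comes from patients with adequate relief, who "showed a reduction in IBSS scores of 87 units". Then: "The power to detect this change at α = .05 in samples of 30 per group is approximately 84" per cent. No SD is given. The text goes on: "In the current study, 45 subjects per group is planned".

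**The concern.** Individual randomisation makes the women independent at baseline. It does not keep them independent once they have spent eight weeks in the same room, with the same leader and the same peers. A strong or weak leader, or a class that gels or does not, moves several outcomes together. Ordinary linear regression treats every woman's residual as independent. A GEE introduced to handle repeated measures deals with correlation within a woman, not between women in a class.

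Treatment is constant within a class, so positive within-class correlation makes the treatment comparison less precise than these models report. The confidence interval is then too narrow and the p-value too small. The article tests an efficacy hypothesis and also intends its effect estimates to guide the size, design and analysis of later trials, so overconfident error bars would carry forward.

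**Working it through.** **Inputs from the article:** difference 87 IBSS units; α = 0.05 (two-sided assumed, as sidedness is not stated); 30 per group for the power statement; 45 per group planned; at least 6 women per arm to start a class.

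**Inputs assumed:** class size *m* of 6 to 8; residual within-class ICC of 0.01 to 0.10.

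**Step 1. The plan's own figure.** The 84% cannot be reproduced independently because no SD is given. Solving backwards with the normal approximation: *d* = (1.960 + 0.994)/√(30/2) = 0.763, so SD = 87/0.763 ≈ 114. A two-sample t calculation gives *d* = 0.776 and SD ≈ 112. These SDs are implied by the 84% under independence; they are not figures from the article.

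**Step 2. Number of classes.** 45/6 = 7.5, so at most 7 full classes per arm, or about 14 in all.

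**Step 3. Design effect and type I error.** DEFF = 1 + (*m* − 1) × ICC. The unadjusted standard error is too small by a factor of √DEFF, so the actual type I error is 2 × [1 − Φ(1.960/√DEFF)].

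| Women per class | ICC | DEFF | Type I error |
|---|---|---|---|
| 6 | 0.01 | 1.05 | 5.6% |
| 6 | 0.05 | 1.25 | 8.0% |
| 6 | 0.10 | 1.50 | 11.0% |
| 7 | 0.05 | 1.30 | 8.6% |
| 8 | 0.01 | 1.07 | 5.8% |
| 8 | 0.05 | 1.35 | 9.2% |
| 8 | 0.10 | 1.70 | 13.3% |

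**Step 4. Simulation.** The baseline-adjusted regression was simulated with no treatment effect, 45 per arm, a baseline-to-final correlation of 0.5 and 10,000 runs per setting. With classes of 6 (plus one of 3) at ICC 0, 0.02, 0.05 and 0.10, rejection rates were 5.0%, 6.6%, 8.3% and 11.0%. With classes of 8 (plus one of 5) they were 5.3%, 6.2%, 8.7% and 13.0%. These agree with the formula.

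**Step 5. Power with a correct standard error.** Use *n*/DEFF per group in power = Φ(*d*√(*n*/(2 DEFF)) − 1.960), with the back-solved *d*.

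- 30 per group, DEFF 1.30: 30/1.30 = 23.1; power falls from 84% to about 73% (t) or 74% (normal).
- 45 per group, DEFF 1.00: 95%.
- 45 per group, DEFF 1.30: 45/1.30 = 34.6; power about 89%.
- 45 per group, DEFF 1.50: 45/1.50 = 30; power 84%, the quoted figure.
- 45 per group, DEFF 1.70: 45/1.70 = 26.5; power about 79%.

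A DEFF of 1.5 corresponds to an ICC of 0.5/5 = 0.10 at 6 per class, or 0.5/7 ≈ 0.07 at 8 per class.

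**The case against.** Four points can be made against this, and each limits it.

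**No ICC is documented.** A reader might infer that the type I error does exceed 5%. The article does not support that as a fact. The inflation needs an ICC above zero, and at 0.01 it is under one percentage point. The 13% needs both the largest assumed class and the highest assumed ICC.

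**Class size is assumed.** A reader might take 6 to 8 per class as stated. Only the minimum of 6 is; the range 4–8 in Randomization is the block size. The Discussion reports 21 withdrawals among 87 women, 10 of them before any class. If a class of 6 shrank to 6 × 66/87 ≈ 4.6, DEFF at ICC 0.05 would be 1 + 3.6 × 0.05 ≈ 1.18 and the type I error about 7%. Larger classes are equally possible, as no maximum is given.

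**Power.** A reader might conclude that the trial is underpowered because 84% drops to about 73%. That drop is for 30 per group, and 45 are planned. At DEFF 1.30 the planned size still gives about 89% before dropout, so the power argument largely falls.

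**The models may be fuller than described.** The article does not name the GEE cluster unit, and an unseen analysis plan could add a class term. But the article itself fixes the primary model as a regression on baseline and gives repeated measures as the only reason for GEE. As stated, neither model accounts for class.

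It is also fair that feasibility is the declared primary aim. That lowers the stakes, but the efficacy hypothesis is still tested.

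**Conclusion.** The point holds in conditional form. Treatment is delivered in interacting groups in both arms, the named models leave out class-level correlation, and if there is any, the treatment standard error is too small and the 5% test is anti-conservative. Under the assumed 6 to 8 women per class and ICC of 0.01 to 0.10, the type I error is about 5.6% to 13%, and about 8.6% in the middle of that range. Raising the sample from 30 to 45 per group protects power up to a design effect of 1.5 before dropout, but corrects neither the standard error nor the type I error. That the 84% assumed independence is a reasonable inference from the absence of a design effect; it cannot be confirmed without the SD. This should be fixed before the final analysis, which the Discussion says is not yet available. With the ICC unknown and possibly small, it does not by itself invalidate the trial.

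**What to change.** - **Models.** Add a random intercept for assigned class to the baseline-adjusted primary model and to the longitudinal model, in both arms. Define class by arm and by the cohort into which each woman was randomised, not by attendance, so that women who never attended stay in the intent-to-treat analysis.
- **Inference.** Use Kenward-Roger or Satterthwaite degrees of freedom. Class-clustered GEE is an alternative only with a small-sample correction, since about 14 classes are too few for an uncorrected sandwich variance.
- **Power text.** State the assumed ICC and class size, and give the power for the planned 45 per group with the design effect included.
- **Reporting.** Report the estimated ICC with its interval. It will be wide: with 14 classes of 6 and a true ICC of 0.05, its standard error is roughly (1 − 0.05)(1.25)√[2/(6 × 5 × 13)] ≈ 0.085. It is a rough guide for a later trial, not a planning value to rely on.

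The cost is one model term, a few sentences and a somewhat wider confidence interval. Cohort and arm should be recoverable from the date-stamped randomisation record together with the class start dates. If the ICC is near zero, little precision is lost.
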